
**D.4 Phase II: To conduct a group randomized controlled trial to evaluate the Patient Navigator Program.**

### **D.4.1 Overview of Methods**

The goal of Phase II is to test whether a Patient Navigator Program implemented in the Tampa Bay region will lead to improved timeliness of cancer care, appropriateness of cancer care, and patient satisfaction. After careful consideration of several study designs for scientific rigor, feasibility, and acceptability by our community, we have selected a group randomized design (D.4.2), with the “group” being a community health center. The intervention arm will receive the Navigator Program first, and the control arm will receive the intervention, but delayed in time to permit the evaluation of program effectiveness. Patients within groups will be recruited by Clinical Research Assistants at the time of a suspicious screening result for cancer of the breast or colorectum (D.4.3). The Patient Navigators will assist the patients who have abnormal screening findings obtain timely appointments, referrals, and financial support that may be necessary. Data will be collected from medical records regarding timing of care and adherence of care to NCCN guidelines [82, 83] with chart abstractions occurring at 12 months, and patient satisfaction occurring for a randomly chosen subsample at baseline and again at 3 months. Data will be collected to assess, among other things, the patient’s navigation through, and satisfaction with, the health care delivery system (D.4.4).

### **D.4.2 Group Randomized Design**

Five clinics will initially be participating in the randomized evaluation of the Navigator intervention: three funded by the Suncoast Community Health Center, Inc, and two by Tampa General Healthcare. Three of the five will be assigned to the initial Navigator intervention, while the other two will receive this intervention later after the evaluation is complete. In order to assure that each participating organization can feel that its patients are benefiting from the organization’s participation in this project, the randomization will assure that at least one clinic affiliated with each organization is chosen for the immediate intervention. Thus we will design the randomization schema to assure that two of the three Suncoast clinics, and one of the two Tampa General clinics receive the immediate Navigator intervention.

Seven additional clinics have been recruited to the study and have been randomized as described above.

###### **D.4.3 Patient Recruitment**

As described previously, seven clinics will provide the Navigator Program and five clinics will not provide the Navigator Program based on random assignment. A description of the Navigator Program to be provided at those clinics randomized to this condition follows. We will make no attempt to alter the delivery of services at those clinics not randomized to deliver the Navigator Program. Rather, we will use both observational and survey methods to characterize the processes that typically occur in these clinics once patients are identified as having a breast or colorectal abnormality. These data will be used to characterize the extent to which delivery of care differed in our two intervention conditions.

The eligibility criteria were defined in D.2.1 above. Subjects having cancer-related abnormalities will be identified by research assistants using a variety of methods. Methodologies for identifying patients will be refined and pilot tested in the project’s first year. Procedures for subject identification and recruitment will be identical for intervention and control clinics. Once identified, patients will be contacted by research assistants for recruitment into the study. Research assistants will use the following sources to identify patients:

*Appointment records*: Appointment records provide the reason for each patient’s visit and will be assessed weekly by research assistants. This information will be used to identify cancer related symptoms (i.e. breast lumps, rectal bleeding).

*Screening logs*: Participating clinics maintain screening logs to document completion of cancer screening tests such as Pap smears, mammograms, and FOBT. Research assistants will track screening logs on a weekly basis to identify patients having abnormal results on mammography or FOBT.

*Referral coordinators*: Research assistants will also make at least weekly contact with referral coordinators at each clinic to identify patients who may have been referred for cancer related problems.

A research assistant assigned to each participating clinic will review medical records in order to identify potential participants who meet these eligibility criteria. Patients found to meet the eligibility criteria will be approached by the research assistant who will first provide a brief verbal explanation of the study. Patients wishing to receive more information will then be provided with a copy of the informed consent form to review. The research assistant will remain available to answer any questions. Those patients wishing to participate will then be asked to sign the informed consent form. Participants will then undergo study procedures as described below.

*Lifetime Cancer Screening*: We will also identify eligible subjects by reviewing results of mammography screening services provided by Lifetime Cancer Screening, either on site or through mobile screening vans. Subjects meeting eligibility criteria will be recruited into the navigation arm if they are patients of intervention clinics or recruited into the control arm of the study if patients of control clinics.

**D.4.4 Description of the Navigation Program**

The goal of the Navigator Program is to facilitate timely access to needed patient care interventions for patients exhibiting abnormal findings related to a breast or with a colorectal cancer screening abnormality. The principles that drive an effective navigation plan of intervention are based on patient/family assessment of needs, development and implementation of a plan of action and evaluation of outcomes. Additionally, a well- integrated Navigation Program with our partner agencies is needed to assure a seamless, well-coordinated program is established where the full scope of resources within the agencies, the cancer center and the community are utilized to meet patient needs. We envision that the navigator assigned at the community health center level will be well integrated into the existing site systems and well acquainted with community resources. The navigator will collaborate on a day-to-day basis with the health center interdisciplinary team, including health center outreach workers, financial advisors and clinical staff performing case management services.

Once a patient is enrolled in the study at a clinic randomized to provide the Navigator Program, the following activities become activated as part of the processes used to navigate the patient into and through the system. Simply put, the navigator helps the patient become informed about the various services, coordinates the care and assists them with decision-making tools. Key to the success of the navigator role is awareness of the availability of resources and creating meaningful and timely linkages. This role involves coordination of services, education and support offered in a highly personal and customized manner to help patients and families through this journey. The navigator provides an important access point to a wide array of services in a coordinated fashion that reduces the ‘shopping’ for providers and services. Specific tasks to be taken on by the patient navigator include the following:

- Effectively utilizes patient assessment tool to identify barriers to timely health services including transportation, health insurance funding, psycho-social needs, health education needs, child care needs, cultural or belief system barriers, unemployment, etc.
- Develops and implements intervention plan to assist patients and families in accessing, seamless, coordinated care based on identified needs, e.g. timely appointments, transportation services, referral to social services, etc.
- Participates with the primary care and cancer team.
- Follows up with patients who missed appointments to assure all barriers to care are addressed as needed.
- Accompanies patient and family to appointments when necessary, serving as a “cultural translator” and patient advocate when appropriate.
- Serves as a liaison between the community and cancer centers/specialists.
- Provides emotional and spiritual support as needed to patient and family.
- Provides (makes) appropriate referrals and linkages to cancer center and community resources; assists patients with securing financial benefits and entitlements.
- Utilizes interventions and strategies that are appropriate to the population, i.e., considering culture, literacy, language, age and gender.
- Evaluates interventions and outcomes continuously and then reformulates plan of action based on responses and needs.

While protocols will be established to guide the navigator in this systems role, there is also a keen focus on client-centered care. In summary, the navigator serves as a constant, that is, a person who consistently guides the patient through the system. The navigator is someone who can piece together complex information in logical and easy-to-understand ways to achieve timely and appropriate access to vital cancer care.

### **D.4.5 Data Collection**

**Data accrual**

We will collect information on the number of subjects who are referred into the study, the number who are successfully consented, and the reasons that referred subjects are not enrolled (couldn’t be contacted, not eligible, declined, etc.).

**Navigated subjects**

The following data will be collected on navigated patients.

*Demographic Survey*

Navigated patients will provide information on demographic characteristics that are unlikely to be found in the medical record. This information will be collected in person by the navigator at the time subjects provide consent. See Demographic Survey for description of individual items.

*Measures of health literacy*

We will administer the REALM (long version) to English speaking subjects at baseline as our standard measure of health literacy. For Spanish speaking subjects, we will administer the 50 item SAHLSA instrument, also at baseline.

Measures of depression

As a potential barrier to receiving cancer related health care, participants will be screened for depression using the PRIME-MD Patient Health Questionnaire (see attached copy of instrument).

*Additional instruments*

For subjects with non cancer diagnoses, the following instruments will be administered within three months of diagnostic resolution: **Impact of Events Scale**, **Communication and Attitudinal Self-Efficacy** (CASE) general scale, **satisfaction with care survey**, **satisfaction with navigator survey**. These instruments and instructions for how they are administered are found in the NOVA Data Dictionary.

For navigated subjects with a diagnosis of cancer, the following instruments will be administered three months after initiation of treatment; Impact of Events Scale, Communication and Attitudinal Self-Efficacy (CASE) cancer scale, satisfaction with care survey, satisfaction with navigator survey.

Chart abstractions will be performed on the medical records of navigated patients approximately three months after diagnostic resolution (three months after initiation of treatment for cancer patients). Information that will be abstracted is described in the NOVA Data Dictionary

Patient demographics Table 2

Patient / Family Medical History Table 3

Charlson Comorbidity Table 4

Breast related outcomes Table 7

Colorectal related outcomes Table 9

For persons diagnosed with cancer, we will also obtain data from the treating hospital tumor registry if possible.

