| Clinic Name | Screening Visits  # per year | African American  (%) | Hispanic  (%) | Under-insured  (%) | Low literacy  (%) | Spanish speaking  (%) |
| Ruskin | 33,800 | 5 | 50 | 85 | 40 | 30 |
| Plant City | 26,000 | 30 | 40 | 85 | 65 | 45 |
| Dover | 36,400 | 0 | 75 | 100 | 50 < 6th gr | 75 |
|  |  |  |  |  |  |  |
|  |  |  |  |  |  |  |
| Health Park | 20,800 | 40 | 20 | 70 | 40 | 5 |
| Midtown | 19,500 | 35 | 35 | 85 | 30 | 5 |

Since the start of the project, the number of participating clinics has increased (n=12) and they have been randomized as described below. Note that randomization occurred within sponsoring organization and for organizations with an odd number of clinics randomization was performed to insure that there were a greater number of intervention clinics than control.

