**Control subjects**

The following data will be collected on control subjects.

*Demographic Survey*

Control patients will provide information on demographic characteristics that are unlikely to be found in the medical record. This information will be collected in person by the research assistant at the time subjects provide consent. See **Demographic Survey** for description of individual items.

*Measures of health literacy*

We will administer the REALM (long version) to English speaking subjects at baseline as our standard measure of health literacy. For Spanish speaking subjects, we will administer the 50 item SAHLSA instrument, also at baseline.

*Additional instruments*

For subjects with non cancer diagnoses, the following instruments will be administered within three months of diagnostic resolution: **Impact of Events Scale**, **Communication and Attitudinal Self-Efficacy** (CASE) general scale, **satisfaction with care survey**, **satisfaction with navigator survey**. These instruments and instructions for how they are administered are found in the NOVA Data Dictionary.

For control subjects with a diagnosis of cancer, the following instruments will be administered three months after initiation of treatment; Impact of Events Scale, Communication and Attitudinal Self-Efficacy (CASE) cancer scale, satisfaction with care survey, satisfaction with navigator survey.

Chart abstractions will be performed on the medical records of control patients approximately three months after diagnostic resolution (three months after initiation of treatment for cancer patients). Information that will be abstracted is described in the NOVA Data Dictionary

Patient demographics Table 2

Patient / Family Medical History Table 3

Charlson Comorbidity Table 4

Breast related outcomes Table 7

Colorectal related outcomes Table 9

For persons diagnosed with cancer, we will also obtain data from the treating hospital tumor registry if possible.

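### The demographic survey taken at consent is given to the navigator in the intervention arm and to a research assistant in the control arm, which puts the person delivering the intervention at the consent encounter in one arm only

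*Protocol*

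**What the plan says.** D.4.5 has parallel subsections for the two arms. For navigated patients, on the demographic survey: "This information will be collected in person by the navigator at the time subjects provide consent". For control patients: "This information will be collected in person by the research assistant at the time subjects provide consent". Apart from the staff member, the arrangement is the same.

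Other sections describe recruitment without distinguishing the arms:

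- D.4.1: "Patients within groups will be recruited by Clinical Research Assistants at the time of a suspicious screening result".
- D.4.3: "Once identified, patients will be contacted by research assistants for recruitment into the study", and "Patients found to meet the eligibility criteria will be approached by the research assistant". The research assistant then explains the study, supplies the consent form and stays to answer questions. One is assigned to each participating clinic.
- D.4.3 also states: "Procedures for subject identification and recruitment will be identical for intervention and control clinics".
- D.4.4 starts the navigator's activities at a defined moment: "Once a patient is enrolled in the study at a clinic randomized to provide the Navigator Program".

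On allocation, D.2 reports that "the number of participating clinics has increased (n=12) and they have been randomized as described below" and lists each clinic with its arm. D.4.7.b restricts the intent-to-treat comparison to patients who have consented and been registered.

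**The concern.** When clinics are randomised and patients enrolled afterwards with the arm known, randomisation does not protect the step at which patients enter. Comparability then depends on that step being run the same way in both arms. A navigator's job is to remove barriers, arrange appointments and give support. If that person is present at consent in one arm, willingness to enrol and the mix of patients enrolled could differ between arms for reasons unrelated to any effect of navigation. Intent-to-treat cannot repair this, because patients who do not consent are outside the analysis.

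A second, smaller issue is measurement. The survey is meant for characteristics that the medical record is unlikely to hold. If different types of staff collect those items in the two arms, a baseline difference could reflect the collector rather than the patients, and for most of these items the chart offers no independent check.

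**Working it through.** The point rests on the text, not on a figure. The passages are set side by side first; a bounded illustration follows.

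**Passages compared**

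1. Who approaches and takes consent: a research assistant in both arms (D.4.1, D.4.3).
2. Who collects the demographic survey at consent: the navigator in the intervention arm, a research assistant in the control arm (D.4.5).
3. When navigator activity begins: after enrolment (D.4.4). Item 2 has the navigator meeting the patient at consent, so items 2 and 3 do not fit together as written.
4. Whether the arm is known at that moment: yes. The 12 clinics are listed as 7 intervention and 5 control (D.2), patients enter the arm of their clinic (D.4.3), and control-site staff are told about the study (D.4.6a).
5. Who is analysed: consenting, registered patients (D.4.7.b).
6. Whether a stated safeguard covers this step: D.4.6b covers selective referral by providers only. D.4.5 records numbers referred and consented and reasons for non-enrolment. D.4.7.b compares refusers with consenters on demographics. None of these specifies a comparison by arm.
7. Where consent happens: in person in D.4.3 and D.4.5. E.2.1 instead describes a mailed letter, a telephone call, verbal consent and a signed form returned by post.

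**The plan's own figures.** D.4.7.b gives 29 and 112 per group for differences of 10 and 5 days (SD 15, one-sided 0.05, 80% power). A t-test calculation gives 28.5, rounded up to 29, and 112.0. Both reproduce.

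**Illustration of size; all inputs on consent are assumptions.** Let c0 be the consent proportion without the navigator present, c1 the proportion with, and D the difference in mean interval between the extra patients and the rest. The shift in the arm mean is (c1 − c0)/c1 × D. With D = 10 days:

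- 70% to 80%: 0.10/0.80 × 10 = 1.25 days
- 70% to 85%: 0.15/0.85 × 10 = 1.76 days
- 60% to 80%: 0.20/0.80 × 10 = 2.5 days

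These are 25% to 50% of the 5-day difference in D.4.7.b, or 12.5% to 25% of its 10-day difference. They scale with D, and with c1 = c0 the shift is zero.

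**Consequence if a shift favoured navigation.** Take no true effect, SD 15, equal groups and the one-sided 0.05 test, with effective total sizes 121 and 402 (the extremes of the D.4.7.b table). The standard error is 15 × √(4/N), which is 2.73 or 1.50 days. The rejection probability is Φ(shift/SE − 1.645):

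| Shift (days) | N = 121 | N = 402 |
| --- | --- | --- |
| 1 | 0.10 | 0.16 |
| 2 | 0.18 | 0.38 |
| 3 | 0.29 | 0.64 |

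A shift the other way would hide a real benefit instead.

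**The case against.** The strongest reply is that the navigator only completes a form. D.4.5 gives the navigator one task, and D.4.1 and D.4.3 give approach, explanation and consent to research assistants everywhere. The survey could be taken straight after signature. The identical-procedures statement concerns identification and recruitment, whereas the staffing difference appears under data collection, so both could be true. This largely stands. A reader might infer that the two arms have different recruiters, or that the navigator offers help as part of the invitation; the protocol does not say so. A reader might also infer that the navigator collects all baseline data. Only the demographic survey is assigned; D.4.5 names nobody for the literacy tests or the depression screen.

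There are also checks that do not depend on who held the survey. The variable table in D.3.3.1 takes age, gender, race-ethnicity, marital status, employment and insurance from the clinic record as well as from interview, and comorbidity from the clinic record. D.4.5 plans the same chart abstraction in both arms. The primary outcome comes from recorded clinical dates, so the survey collector does not affect its measurement. These points stand too, but such checks detect an imbalance after the event and do not prevent it.

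Finally, with open allocation, patients at intervention clinics are invited to a study that offers navigation whoever completes the form, so uniform staffing may leave some difference in consent. That is right, and it limits what the fix can achieve. It is no reason to keep an arm-dependent step that is easily removed.

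**Conclusion.** The point holds in a narrow form. The protocol specifies an arm-dependent staffing rule at the time of consent. That rule conflicts with navigation starting after enrolment and weakens, without flatly contradicting, the statement of identical recruitment. With open clinic allocation and an analysis set defined by consent, it creates an avoidable risk of differential enrolment, and of differential collection of survey items that the chart does not hold.

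A reader might go further and conclude that enrolment does differ by arm or that the result is biased. The documents do not support that: they give no consent rates by arm, and the day shifts above rest wholly on assumed rates and an assumed 10-day difference. Hard-to-reach extra patients would push the result toward the null, and engaged ones toward apparent benefit. The navigator's presence at consent is itself uncertain, since the mail and telephone route in E.2.1 has nobody physically present. The amendment is worth making; the inconsistency does not by itself invalidate the design.

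**What to change.** - Amend the demographic-survey sentence for navigated subjects in D.4.5 to match the one for control subjects, so that a research assistant completes the survey in both arms.
- State that the navigator's contact with the patient starts only after the signed consent and the completed survey are logged. This agrees with D.4.4.
- Reconcile D.4.3, D.4.5 and E.2.1 on whether consent is taken in person or by mail and telephone, and apply the same route in both arms.
- Report the referral, consent and non-enrolment counts already planned in D.4.5 by arm and by clinic.

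The cost is a short amendment and one hand-over step from research assistant to navigator. D.4.3 already assigns a research assistant to each clinic, and the counts are already to be collected. The change does not remove any difference in consent that arises from open allocation itself; reporting consent by arm and clinic is what would show it.

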**Control subjects**

The following data will be collected on control subjects.

*Demographic Survey*

Control patients will provide information on demographic characteristics that are unlikely to be found in the medical record. This information will be collected in person by the research assistant at the time subjects provide consent. See **Demographic Survey** for description of individual items.

*Measures of health literacy*

We will administer the REALM (long version) to English speaking subjects at baseline as our standard measure of health literacy. For Spanish speaking subjects, we will administer the 50 item SAHLSA instrument, also at baseline.

*Additional instruments*

For subjects with non cancer diagnoses, the following instruments will be administered within three months of diagnostic resolution: **Impact of Events Scale**, **Communication and Attitudinal Self-Efficacy** (CASE) general scale, **satisfaction with care survey**, **satisfaction with navigator survey**. These instruments and instructions for how they are administered are found in the NOVA Data Dictionary.

For control subjects with a diagnosis of cancer, the following instruments will be administered three months after initiation of treatment; Impact of Events Scale, Communication and Attitudinal Self-Efficacy (CASE) cancer scale, satisfaction with care survey, satisfaction with navigator survey.

Chart abstractions will be performed on the medical records of control patients approximately three months after diagnostic resolution (three months after initiation of treatment for cancer patients). Information that will be abstracted is described in the NOVA Data Dictionary

Patient demographics Table 2

Patient / Family Medical History Table 3

Charlson Comorbidity Table 4

Breast related outcomes Table 7

Colorectal related outcomes Table 9

For persons diagnosed with cancer, we will also obtain data from the treating hospital tumor registry if possible.

*Additional sources of medical information*: For subjects who received treatment at the Lifetime Cancer Screening Center or the H. Lee Moffitt Cancer Center, we will supplement primary care clinic chart reviews with additional sources of information. Clinical records from Moffitt (PowerChart) will be reviewed for data elements that are missing from primary care records. In addition, for subjects who received cancer care at the Moffitt Cancer Center, the Moffitt Cancer Registry will be queried to determine all aspects of subjects’ first course of cancer treatment.

The following instruments were later added to be conducted among study participants. These are self-reported surveys to evaluate psychosocial determinants of health. These surveys are to be administered shortly after diagnostic resolution and, if the patient is diagnosed with cancer, three months following the initiation of treatment:

1. PHQ Depression
2. Perceived Stress Scale
3. Cancer Worry Scale
4. Cancer Risk Scale
5. Cancer Response Efficacy Scale
6. Brief COPE
7. Pearlin Mastery (Perceptions of Control)
8. ISEL Social Support
9. Use of Tobacco/Alcohol
10. IPAQ Physical Activity
11. Preventive Health Behaviors
12. FACT B or C
13. Multidimensional Fatigue Symptom Inventory

